
#### Implementation process assessment

As suggested by Hawe *et al*., we will assess how the intervention was implemented in the context [75]. Follow-up sheets for the “sessions” carried out will make it possible to count the number of sessions and the participation of all the actors. Semi-structured interviews will be carried out at the end of the intervention with representatives of actors that have participated in the implementation of the intervention (e.g., teachers, associative staff, project managers). These interviews will make it possible to obtain qualitative information on how the study was implemented, and what the facilitators/breaks were in the implementation. In addition, an intervention monitoring grid will make it possible to identify the achievement (done/not done, why?) of the intervention modules; an intervention monitoring sheet will be drawn up including all the sessions scheduled for the teachers and associative staff and will be completed and monitored by the project manager who will centralize the information.

#### Feasibility study

One preliminary pilot study has been conducted to confirm that schools and classes recruitment was feasible and that to check the participating children and parents understood and answered the evaluations. This pilot study targeted 111 children from two communes of the Var department (Toulon and Laroquebrussane). Children were aged from 7 to 11 years old attending four public schools. Among the targeted population, 100 children and their parents accepted to participate resulting in 90% of the acceptance rate. We found that the procedure for distributing and collecting accelerometers was feasible, with 78 children and their parents giving their consent for the children to wear the accelerometer for seven consecutive days (i.e., 78% of acceptance rate). We also confirmed the feasibility of the parents’ questionnaire, with 64% of the completion rate. In class, the administration of children’s questionnaires was feasible (evaluating lifestyle habits, TCM variables and quality of life) resulting in approximately one hour for the completion of the questionnaire for a class of 20–25 children.

### Statistical considerations

#### Sample size calculation

In a French study measuring ST with Actigraph GT3X accelerometers, children aged 7 to 10 accumulated 583 minutes on average (standard deviation: 57 min) of ST per day [76]. We will aim with the CIPRES intervention to reduce by 30 minutes per day the ST in the target population. To evaluate the number of subjects needed, we will choose α risk equal to 5% and β risk equal to 10% (power = 90%). Without considering clusters, showing a decrease of 30 minutes of ST per day between pre- and post-intervention will require to include 92 children per group (taking into account a correlation of 0.4 between baseline and follow-up measures). Randomization by cluster requires taking into account inflation factor of our sample size because of the homogeneity of the conditions within each cluster: 1+(m(1+cv^2^)-1)r (m being the average number of subjects per cluster, cv a coefficient of variation equal to the ratio between the standard deviation of the size of the clusters per m, and r being the intraclass correlation coefficient). In our study, the cluster is a municipality. With a potential average of 150 children included per municipality, a coefficient of variation at 0.5, and a rho coefficient set at 0.01 according to databases of intraclass correlation coefficients [77] and a recent French study [78], the inflation factor is equal to 2.87. The number of subjects needed to be able to show a difference of 30 minutes per day in ST is estimated at 527 children. Taking into account a potential rate of 25% of lost-to-seen over time, the number of subjects to include in the CIPRES study amounts to 700 children (i.e., 350 in the intervention group and 350 in the control group), corresponding to approximately 14 classes per group (i.e., approximately 7 schools per group).

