**Methods:**

The CIPRES study is a cluster-randomized controlled trial comparing intervention vs control groups. A total of 700 children are targeted for inclusion, distributed in four municipalities considered as clusters. The study consists of two successive phases: 1) co-building of a SB prevention intervention by using a participatory approach involving representatives of each level of the SEM (e.g., children, parents, staff from municipalities, teachers) and 2) implementation and evaluation of the intervention. The intervention will last for 6 weeks in each involved class. Primary outcome will be the sedentary time of children per week, assessed by accelerometry. In addition, children and their parents will be asked to fill out questionnaires concerning children’s physical activity level, screen time, quality-of-life and variables of the TCM.

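### The inflation factor uses 150 children per municipality, a size that does not fit 700 children in four municipalities; 2.87 and 527 should be restated for about 131 analysed per municipality

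*Protocol article*

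**What the plan says.** Under Sample size calculation, the protocol article starts from a cited French study in which children accumulated "583 minutes on average (standard deviation: 57 min) of ST per day". It aims to "reduce by 30 minutes per day the ST in the target population", with α 5% and power 90%. Before clustering, this "will require to include 92 children per group", "taking into account a correlation of 0.4 between baseline and follow-up measures".

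The inflation factor is 1 + (m(1 + cv²) − 1)r, where m is the mean number of subjects per cluster and the cluster is the municipality. The inputs are m ("With a potential average of 150 children included per municipality"), cv = 0.5 and r = 0.01. The stated results are an inflation factor of 2.87 and 527 children needed. After a 25% loss, "the number of subjects to include in the CIPRES study amounts to 700 children", split 350 and 350.

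The number of clusters is fixed elsewhere. The abstract states: "A total of 700 children are targeted for inclusion, distributed in four municipalities considered as clusters". The Study design and Population sections name the four municipalities, and the Population section gives their allocation, two per arm.

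**The concern.** When the number of clusters is open, mean cluster size is a planning input. Here the four municipalities are named, so mean cluster size is set by the total: m = N/4. The paragraph puts in 150 and ends with a design whose mean cluster size is 175 at inclusion and about 131 at analysis. The inflation factor it reports is therefore not that of the trial it describes.

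The inflation factor, the evaluable number, the enrolment target and the 90% power are the article's justification for the size of the trial. With four clusters, every added child raises the inflation factor, so the required number is sensitive to m. A reader who wants the power of 525 evaluable children in four municipalities cannot take it from the paragraph as written.

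**Working it through.** **Inputs** (all from Sample size calculation, except the four municipalities, which are in the abstract, Study design and Population): SD 57, difference 30, correlation 0.4, α 0.05, power 0.90, cv 0.5, r 0.01, loss 25%, four clusters. The article does not say whether the test is one- or two-sided. Two-sided is assumed because it reproduces 92 per group; one-sided gives 75.

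**Reproducing the plan's figures**

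1. SD of the change score: 57 × √(2 × (1 − 0.4)) = 62.44.
2. Per group: 2 × (1.96 + 1.2816)² × 62.44² / 30² = 91.04, rounded up to 92, so 184 in total. Other variance choices do not give 92: the raw SD gives 76 and a baseline-adjusted SD gives 64.
3. Inflation at m = 150: 1 + (150 × 1.25 − 1) × 0.01 = 2.865, stated as 2.87.
4. Evaluable: 184 × 2.865 = 527.2, stated as 527.
5. Included: 527/0.75 = 703, stated as 700.

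There is no slip inside this chain.

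**Checking m against the design**

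- Included: 700/4 = 175.
- Analysed: 0.75 × 700 = 525, and 525/4 = 131.25.
- Implied by m = 150: 4 × 150 = 600 children. If 150 meant analysed children, that would be 600 analysed and 600/0.75 = 800 included. Neither agrees with 527 or 700.

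**Inflation and power for the stated design, on analysed children**

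- Inflation at m = 131.25: 1 + (131.25 × 1.25 − 1) × 0.01 = 2.63.
- Effective number per arm: 262.5/2.63 = 99.8.
- Standard error of the difference: 62.44 × √(2/99.8) = 8.84.
- Standardised difference: 30/8.84 = 3.39.
- Normal-approximation power: Φ(3.39 − 1.96) = about 92%. The same calculation with m = 150 gives about 90%.

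**Number needed for 90% when m = N/4 is imposed**

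The formula can be written as 0.99 + 0.0125m, so N = 184 × (0.99 + 0.0125 × N/4) = 182.16 + 0.575N. This gives N = 182.16/0.425 = about 429 evaluable (m about 107, inflation 2.33) and 429/0.75 = about 572 included.

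**Allowing for four clusters**

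The calculations above use a normal reference, as the plan does. With two municipalities per arm, inference at the randomised unit has 4 − 2 = 2 degrees of freedom. Keeping the standardised difference of 3.39 and taking the noncentral t distribution on 2 degrees of freedom, power is about 46%.

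**The case against.** The strongest reply is that the figures follow from their stated inputs, that 150 is called a potential average, and that it lies between 131 and 175. The first part stands: 92, 2.87, 527 and, to within rounding, 700 all reproduce, so this is not a calculation error. The second does not rescue the figure. A loose planning average is reasonable when the number of clusters is open, but here it is fixed and so is the total.

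A second reply is that 150 is on the safe side. On analysed children that is right: 2.87 exceeds 2.63, and the nominal power is higher than claimed.

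A reader might go the other way and infer that the trial is undersized, because the paragraph speaks of included children and 175 exceeds 150. Putting m = 175 into the formula gives 3.18, 585 evaluable, 780 included, and about 87% power with 525 evaluable. The document does not support that conclusion. Its wording is not strict: the same paragraph uses the verb include for the 92 per group, before clustering or loss enters. The inflation factor applies to the children who enter the analysis. Nor is 780 a consistent solution, since it implies 195 per municipality, not 175; solving jointly with m as enrolled children gives about 1,041. The one-step figure at m = 131 (484 evaluable, 645 included) fails the same test, because 484/4 = 121. These figures should not be presented as a range of valid answers.

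Finally, the correction alone changes no decision and would print a higher power. That is a fair warning, and it is why the restatement must not stand by itself.

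**Conclusion.** The point holds as an input that is inconsistent with the design. The mean cluster size of 150 fits neither the 175 included nor the about 131 analysed children per municipality that 700 children in four municipalities imply. Under the plan's own method, the inflation factor for the stated design is 2.63, not 2.87. The evaluable number for 90% power is about 429 (572 included), not 527, and 525 evaluable give about 92%.

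These results rest on a two-sided 5% test, a change-score variance, cv 0.5, r 0.01, equal arms and a 25% loss spread evenly over municipalities. They do not show that 700 is too small. They are also no reason to enrol fewer, because the normal approximation behind them makes no allowance for two clusters per arm. With that allowance, nominal power falls from about 92% to about 46% under the same inputs. The cluster count is a separate and much larger matter than the choice of m. The mismatch is worth correcting because it sits in the stated justification for the trial's size and the correction is cheap.

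**What to change.** In Sample size calculation, state that m is the mean number of analysed children per municipality, 525/4 = about 131. Replace 2.87 with 2.63, and stop presenting 527 and 700 as derived from m = 150. Then state the power that 700 included (525 evaluable) provides, leaving enrolment unchanged.

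In the same edit, give that power with allowance for four clusters and 2 between-cluster degrees of freedom (about 46% under the plan's inputs), next to the normal-approximation figure of about 92%. The latter should not appear alone.

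The cost is a rewrite of one paragraph: no extra children and no change in conduct.

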### Population

The targeted territories are four cities from southeast France next to the Mediterranean Sea (Var department) randomly assigned to intervention group (Toulon, Brignoles) or control group (La Seyne-sur-Mer, Hyères). The target population is made up of 700 children attending primary schools in these municipalities in the years 4 and 5 classes (aged 8 to 10 years old). This study will more broadly include the participation of key actors who are in contact with children or likely to play a role in the organization of school, extracurricular and family time for children, namely teachers (school time), educators including association staff and municipal staff (extracurricular time), and the parents of children (family time). The schools will be selected with the help of pedagogical advisors of the French National Education and then be contacted by the Health Education Committee of the Var department (the CODES 83). Schools and then classes will be recruited within the included municipalities, on a voluntary basis. For each class willing to participate in the study, parents receive a written note which includes explanations about the research’s aims, the assessment methods (i.e., self-administered questionnaires for children and their parents, and accelerometers worn by children for 7 days at T0 and T1), and that participation is based on their own volition. Children are given consent forms to take home for their parents to sign. Parents have the choice of ticking three types of consents: (i) parents’ consent to filling in the questionnaires; (ii) parents’ consent to children filling in the questionnaires; (iii) parents’ consent to children wearing accelerometers. Only children whose parents have given their consent will be included (Fig 2).

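### The stated 90% power is not delivered: two municipalities per arm leave 2 degrees of freedom, and power at the plan's own inputs is about 43–46%

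*Protocol article*

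**What the plan says.** All references are to the protocol article.

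- **Randomised unit and number of clusters.** The abstract (Methods) describes the children as "distributed in four municipalities considered as clusters". The Population section names the towns as "randomly assigned to intervention group (Toulon, Brignoles) or control group (La Seyne-sur-Mer, Hyères", so there are two clusters per arm. Study design and Sample size calculation both confirm that the cluster is the municipality.
- **Error rates and target.** Sample size calculation states: "we will choose α risk equal to 5% and β risk equal to 10% (power = 90"%). The target effect is given as "We will aim with the CIPRES intervention to reduce by 30 minutes per day the ST in the target population".
- **Inputs.** The reference study's children "accumulated 583 minutes on average (standard deviation: 57 min) of ST per day". The size before clustering "will require to include 92 children per group", "taking into account a correlation of 0.4 between baseline and follow-up measures". Clustering enters through an inflation factor with a mean of 150 children per municipality, a coefficient of variation of 0.5 and an intraclass correlation (ICC) of 0.01, reported as 2.87.
- **Result.** "The number of subjects needed to be able to show a difference of 30 minutes per day in ST is estimated at 527 children". With 25% loss this becomes 700.
- **Analysis.** The Statistical analysis section plans a mixed model with random effects for schools, classes and individuals. Municipality is not among them.

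**The concern.** The calculation multiplies an individually randomised sample size by a design effect and stops there. That is adequate when there are many clusters. With four, the between-municipality variance has to be estimated from two towns in each arm, and the test must pay for that uncertainty through a t distribution on 2 degrees of freedom. The sample size section contains no such correction.

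If the power claim is wrong, the reader is told that a real 30 min/day effect would be missed one time in ten when it would be missed more than half the time. The Discussion ties possible wider deployment to these results, so a null finding could be taken as evidence that the intervention does not work. A significant finding from an analysis that borrows degrees of freedom from schools or classes would not have a 5% false-positive rate.

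**Working it through.** **Inputs** (all from Sample size calculation): SD 57 min/day; correlation r = 0.4; difference 30 min/day; α = 5%; power 90%; mean cluster size m = 150; CV 0.5; ICC 0.01; 527 evaluable children. Sidedness is not stated. Two-sided is assumed because it reproduces the plan's 92 per group. The number of clusters, two per arm, is from Population.

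**1. Reproduce the plan.**
- SD of change = 57 × √(2 × (1 − 0.4)) = 62.44.
- n per group = 2 × (1.96 + 1.2816)² × 62.44² / 30² = 91.04, rounded up to 92.
- Inflation = 1 + (150 × (1 + 0.5²) − 1) × 0.01 = 2.865.
- 2 × 92 × 2.865 = 527.
- 527 / 0.75 = 703, against 700 stated.

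The arithmetic is sound for the formula used.

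**2. Standard error and noncentrality at 527 children.**
- SE = 62.44 × √(4 × 2.865 / 527) = 9.21.
- Noncentrality = 30 / 9.21 = 3.26.

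**3. Power from the same SE under the two critical values.**
- Normal, 1.96: 90.3%.
- t on 4 − 2 = 2 df, 4.303: P(noncentral t > 4.303) = **43.4%**.

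Numerical integration of the noncentral t gives these figures. With m = 527/4 = 131.75, the inflation is 2.64, the noncentrality 3.40 and the 2-df power **45.9%**. A simulation of municipality means on that basis gives 46.0%.

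**4. What the design can detect (m = 150).**
- 90% power on 2 df needs a noncentrality of 6.80, so the detectable difference is 6.80 × 9.21 ≈ 63 min/day (60 at m = 131.75).
- 95% interval half-width: 4.303 × 9.21 = 39.6 min/day, against 1.96 × 9.21 = 18.0 with the normal value. At this SE, an observed 30-minute reduction would have an interval that includes zero.

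**5. Sensitivity to the ICC** (527 children, CV 0.5, power on 2 df).

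| ICC | m = 150 | m = 131.75 |
|---|---|---|
| 0 | 78% | 78% |
| 0.005 | 56% | 58% |
| 0.01 | 43% | 46% |
| 0.02 | 31% | 33% |

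**6. Sensitivity to other assumptions at ICC 0.01, on 2 df.**
- Equal cluster sizes: 48% (m = 150) to 50% (m = 131.75).
- All 700 analysed (m = 175, CV 0.5): 49%.
- Baseline-adjusted SD, 57 × √(1 − 0.4²) = 52.24: 55% (m = 150) to 57% (m = 131.75).
- Baseline-adjusted SD with equal cluster sizes: 59% to 62%.
- Size-weighted municipality-level test, by simulation: 55%.

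**7. Can more children help?** As the number of children grows without limit, the SE tends to 62.44 × √(0.01 × 1.25) = 6.98 (CV 0.5) or 62.44 × √0.01 = 6.24 (equal sizes). Power is then capped at 61% or 69%. The shortfall comes from the number of clusters: the same 527 children over three municipalities per arm would give 81%, and over four per arm 92%.

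**The case against.** The strongest points on the other side are these.

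- **The 527 is correct.** It is, for the formula used. The fault is the 90% power attached to it, which makes this a design and inference error rather than a slip of arithmetic.
- **The figure of 43–46% looks too precise.** It assumes a change-score variance and an ICC of 0.01 applying in full to the change. The planned test is a group-by-time interaction, so stable differences between towns cancel, and the article does not say whether 0.01 describes levels or changes. This stands as a caution. Other defensible choices at ICC 0.01 give roughly 48–62%, and an ICC of 0.002 would give 68–69%. None of the 2-df variants tried reaches 90%, and with the change-score variance even an ICC of zero gives 78%.
- **The mixed model would have more degrees of freedom.** On the article's approximate counts of 7 schools and 14 classes per group, taking degrees of freedom from schools (12) or classes (26) would give nominal power of 84.8% or 88.0% at the same SE. That does not rescue the claim. The model omits municipality, so it leaves out or misallocates the between-town variance that the sample size section itself assumes, and its type I error would exceed 5%. If clustering were ignored altogether at an inflation of 2.865, the error rate would be 2 × P(Z > 1.96/√2.865) ≈ 25%.
- **Recruitment is under way.** True, so the correction is to the claim and the interpretation, not to the size of the trial.

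Four towns can be split two and two in only 6 ways, so a randomisation test could not give a two-sided p below 2/6 = 0.33. No such test is planned, so this only illustrates how little information four clusters carry.

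**Conclusion.** The power statement is wrong as written. At the plan's own inputs, a valid two-sided 5% test at the level of randomisation has about 43–46% power for 30 min/day, so a true effect of that size would be missed about 54–57% of the time instead of 10%. The detectable difference at 90% power is about twice the target. The direction is certain because it follows from four clusters in two arms. The exact percentage depends on the ICC, the variance used and the balance of cluster sizes, and should be reported as a range.

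**What to change.** 1. In Sample size calculation, replace the 90% claim with the power on 2 degrees of freedom: about 43–46% at ICC 0.01, with the range over ICC 0.005 to 0.02 (56% to 31% at m = 150, or 58% to 33% at m = 131.75). Use one cluster size throughout.
2. On the same basis, state the difference detectable with 90% power (about 63 min/day at m = 150) and the expected 95% interval half-width (about 40 min/day).
3. In Statistical analysis, bring municipality into the primary comparison, either as a random effect with small-sample degrees of freedom or through a municipality-level analysis. Otherwise the restated power and the planned model would contradict each other.
4. Say that conclusions will rest on the estimate and its municipality-level interval, that a non-significant result will not be read as absence of effect, and that generalisation beyond four towns is limited.

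The cost is wording in the protocol or SAP and a less favourable stated power. No extra children are needed and the intervention does not change. Restoring 90% power would take more municipalities, not more children in the same four.

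### The 14 classes per group do not yield the stated number of children with accelerometer data at the pilot's own rates, and the text does not say which children the 700 counts

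*Protocol article*

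**What the plan says.** All references are to the protocol article.

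- **Sample size calculation.** The need is 527 children. One allowance follows: "Taking into account a potential rate of 25% of lost-to-seen over time". This gives 700 children, 350 per group, "corresponding to approximately 14 classes per group (i.e., approximately 7 schools per group".
- **Effectiveness assessment.** The primary outcome is sedentary time measured by accelerometer over seven days.
- **Population.** "Parents have the choice of ticking three types of consents": the parents' questionnaire, the child's questionnaire, and the child wearing the accelerometer. Inclusion depends on parental consent, but the section does not say which of the three is required. The 700 is called the target population here and under Study design.
- **Feasibility study.** Of 111 pupils targeted, "100 children and their parents accepted to participate resulting in 90% of the acceptance rate". Of those 100, 78 are reported as "giving their consent for the children to wear the accelerometer for seven consecutive days (i.e., 78% of acceptance rate". Questionnaire time is described for a class of 20 to 25 children.

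**The concern.** The pilot is reported immediately before the sample size calculation, yet neither its participation rate nor its accelerometer consent rate enters that calculation. Because accelerometer consent is a separate choice, a child can take part in the study without ever having a value for the primary outcome. The only allowance is worded as loss over time, which does not describe a child who never wears the device.

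The conversion to classes is tighter still: 350 / 14 = 25, so every class must hold 25 pupils who all take part. Recruitment is described as under way. If progress is counted in classes or in total participants, the target could appear met while the number with accelerometer data is well below the number the plan says it needs.

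**Working it through.** **1. The plan's own figures reproduce.** Inputs from Sample size calculation: "accumulated 583 minutes on average (standard deviation: 57 min) of ST per day"; aim to "reduce by 30 minutes per day the ST in the target population"; 5% alpha (two-sided reproduces the figure); 90% power; baseline to follow-up correlation 0.4; average municipality size m = 150; coefficient of variation 0.5; intraclass correlation 0.01.

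- SD of change = 57 × √(2 × (1 − 0.4)) = 62.4
- n per group = 2 × (62.4 × (1.960 + 1.282) / 30)² = 91.04, so 92, or 184 in total
- Inflation factor = 1 + (150 × 1.25 − 1) × 0.01 = 2.865
- 184 × 2.865 = 527
- 527 / 0.75 = 703, stated as 700; conversely 700 × 0.75 = 525

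**2. What 28 classes supply at the pilot's rates.** Accelerometer consent among pupils approached is 78/111 = 70% (0.90 × 0.78).

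| | Classes of 20 | Classes of 25 |
|---|---|---|
| Pupils approached | 560 | 700 |
| With accelerometer consent (× 78/111) | 393 | 492 |
| After 25% loss (× 0.75) | 295 | 369 |

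Both consent totals are below 527 before any child is lost. A class would need 25 / 0.702 = 36 pupils approached, or 25 / 0.78 = 32 participants, to supply 25 children with accelerometer consent.

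**3. What 700 children supply, by reading.**

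- 700 pupils approached: 700 × 0.90 × 0.78 × 0.75 = 369
- 700 participants: 700 × 0.78 × 0.75 = 410
- 700 with accelerometer consent: 700 × 0.75 = 525. This takes 700 / (25 × 78/111) = 40 to 700 / (20 × 78/111) = 50 classes, or about 20–25 per group, and 700 / 0.78 ≈ 900 participants.

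**4. Power under the plan's formula.** The inflation factor depends on m. With four municipalities, m = N/4, so fewer children mean a smaller factor. Power = Φ(30 / (62.4 × √(2/n_eff)) − 1.96), with n_eff = (N/2) / factor.

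| N analysable | m | Factor | n_eff per group | Power |
|---|---|---|---|---|
| 295 | 74 | 1.91 | 77 | 85% |
| 369 | 92 | 2.14 | 86 | 88% |
| 410 | 102.5 | 2.27 | 90 | 90% |
| 525 | 131 | 2.63 | 100 | 92% |

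**5. Sensitivity to the consent rate.** 78 of 100 has a 95% interval of about 69–85%. At 85% and classes of 25, 28 classes give 700 × 0.90 × 0.85 = 536 with consent and 402 after loss. So the shortfall before loss depends on the pilot's point estimate, but the shortfall after loss does not. Even with no refusals at all, 28 classes of 25 give only 525.

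**The case against.** **The 700 may already mean children with the device.** The calculation concerns accelerometer data only, so this reading is fair, and on it the 700 is adequate. It cannot be ruled out, so 410 is not simply what the plan delivers. Against it, the pilot counts 100 as accepting although only 78 agreed to the device, and it uses the same target-population term for its 111 pupils before acceptance. On this reading 14 classes per group is still wrong.

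**The class figure is only approximate.** A reader might infer that recruitment stops at 14 classes per group. No section says so; the figure is a conversion and the target is set in children. But an approximation does not stretch from 14 to 20–25.

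**The trial would be badly underpowered.** A reader might infer this from the gap to 527, or by holding the factor at 2.87, which gives 68–82%. That factor belongs to m = 150 only and cannot be kept when there are fewer children in the same four municipalities. The 527 is itself generous for the same reason: solving N = 184 × [1 + (1.25N/4 − 1) × 0.01] gives about 429. Against that figure, 410 is 4% short and 295–369 are 14–31% short.

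**The pilot is small and not the trial population.** True: 100 participants aged 7 to 11, from two communes, one of them outside the trial, and the 20–25 describes questionnaire sessions. The results are projections, not forecasts.

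**The 25% may cover refusal, or the mixed model may absorb it.** If 22% never consent, 0.78 × 0.96 = 0.75 leaves about 4% for real attrition. The model can use a child with baseline only, but not a child with no accelerometer value at either time.

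**Conclusion.** The point stands as an internal inconsistency in the recruitment figures. The 92, 527 and 700 are computed correctly. The conversion to 14 classes per group conflicts with the article's own pilot: about 295–369 children with the primary outcome at both times, against 527 stated as needed. What the 700 delivers, about 410 or about 525, cannot be settled from the text.

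The consequence is limited: about 85–90% power by the plan's formula, compared with 92% at 525 on the same basis. This rests on the pilot rates carrying over, classes of 20–25, 25% loss in addition to non-consent, an intraclass correlation of 0.01 and the normal approximation. Invalid wear time would lower the counts further; the article gives no rate, so none is applied. The question of having only four municipalities is separate, and extra children would not resolve it.

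**What to change.** Choose one of two restatements in Sample size calculation:

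1. State that the 700 are children with accelerometer consent and correct the class count to about 20–25 per group (about 900 participants at the pilot's rate). This costs roughly 12–22 more classes in total and brings formula power to about 92%.
2. Keep the planned size, say what the 700 counts, and give the expected number with the primary outcome (about 295–410, noting that the rates come from 100 pilot participants) with its power, using an inflation factor that matches the expected municipality size. This costs one recalculation and no extra recruitment; the downside is a slightly less favourable stated power.

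Under either option, state which consent is required for inclusion, and monitor recruitment by the number of children with accelerometer consent rather than by classes or total participants.
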